#### Interim analysis

We do not plan any interim analysis.

## Sample size estimation

In the smartphone psychotherapy intervention used in this study, CBT, including behavioral activation and cognitive restructuring, showed a statistically significant effect among 164 depressive patients, with an effect size of 0.3–0.4. In this study, to determine an effect size of 0.3, for each intervention factor (problem-solving skills, behavioral activation, assertive communication) and its interaction at an alpha = 0.05 and a beta = 0.20, we need a total sample size of 350. We estimated the effect size as 0.3 because problem-solving skills or behavioral activation had the same effect as full-package CBT in a recent comprehensive meta-analysis [45]. To achieve this, the sample size needs to be 22 for each of the 16 combinations, and the total sample size is therefore 16 × 22 =352.

Although we expect a dropout of approximately 20%, we will use mixed-effects repeated measures analysis.

As a study with more than five measurement points is known to require 30–50% fewer participants for the same power compared to a pre-to-post-only assessment, we set the final target sample size of our study conservatively, as estimated above.

If the case accumulation is smoother than expected, we will continue the case accumulation aiming at a sample of 787, which will enable an effect size of 0.2.

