### Statistical analysis and power calculation

#### Primary analyses

We will use the mixed-effects repeated-measures (MMRM) analysis [41] to estimate the mean difference in change scores on the PHQ-9 for each component. We will use the following regression model for the outcome variable of *i*th participant and *j*th visit ($$i=\mathrm{1,2},\dots ,n;j=\mathrm{1,2},\dots ,T$$),$$E\left[{Y}_{ij}\right]={\beta }_{0}+{\beta }_{1}\times B{A}_{i}+{\beta }_{2}\times {AT}_{i}+{\beta }_{3}\times {PS}_{i}+{\beta }_{4}\times visi{t}_{j}+{\beta }_{5}\times ag{e}_{i}+{\beta }_{6}\times se{x}_{i}+{\beta }_{7}\times baseline PHQ{9}_{i}+{\beta }_{8}\times {BA}_{i}\times visi{t}_{j}+{\beta }_{9}\times {AT}_{i}\times visi{t}_{j}+{\beta }_{10}\times {PS}_{i}\times visi{t}_{j}$$where $${Y}_{ij}$$ is the outcome variable, $$B{A}_{i}, {AT}_{i}$$ and $${PS}_{i}$$ are treatment indicators of the three components, and $$visi{t}_{j}$$ is a nominal variable indicating the visit time. For the within-participant covariance matrix model, we will adopt the unstructured structure. We calculated pre–post effect sizes by dividing the estimated mean changes from baseline to week 8 by the observed SD of baseline scores, and between-group effect sizes (SMD) at week 8 by dividing the estimated mean differences in change scores between groups by the observed SD of week 8 scores. No adjustment for multiple testing will be applied in the estimation of the statistical significance of the main and interaction effects in this model, and the conventional threshold for statistical significance (*p* < 0.05, two-sided) will be used because of the following: in the optimization phase of the MOST framework [42], the emphasis is on making a decision about what components will make up the optimized intervention, and factorial designs usually evaluate multiple, completely different interventions that could have been assessed in separate trials and, conventionally, the multiple hypotheses have been tested independently for these trial designs [43, 44].

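### The targets of 352 and 787 carry no allowance for the plan's own 20% dropout, and the repeated-measures saving offered instead does not apply to a week-8 contrast, so the 80% power is unsupported as stated

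*Protocol article*

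**What the plan says.** Under *Sample size estimation* the protocol article sets out "to determine an effect size of 0.3, for each intervention factor", "at an alpha = 0.05 and a beta = 0.20", which gives a total of 350. This is rounded up to the design: "the sample size needs to be 22 for each of the 16 combinations", that is 352. If recruitment goes well, the trial continues, "aiming at a sample of 787, which will enable an effect size of 0.2".

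Dropout gets one sentence: "Although we expect a dropout of approximately 20%, we will use mixed-effects repeated measures analysis". The next sentence supplies the reason for not inflating: "a study with more than five measurement points is known to require 30–50% fewer participants for the same power", compared with a pre-to-post design. On that ground the section says the target was set conservatively.

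The analysis is fixed elsewhere. *Primary outcome measure* names the PHQ-9 score at week 8. *Primary analyses* specifies an MMRM with nominal visit, component-by-visit terms, unstructured within-participant covariance and baseline PHQ-9 as a covariate. Tests are two-sided at 0.05, and the between-group effect size is scaled by the observed SD of week-8 scores.

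**The concern.** A size computed for complete data keeps its stated power under 20% loss only if something else supplies the missing information. The section names one source, the repeated measurements. A saving of that kind belongs to analyses that pool visits, such as a slope or a time-averaged effect. The primary model does neither: each visit has its own component effect, and the contrast of interest is the one at week 8.

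The trial exists to decide which components go into the package, with each main effect judged at p < 0.05. A non-significant component will be read against the claimed 80% power. If that claim lacks a valid basis, a component may be set aside with more confidence than the design earns.

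**Working it through.** **Inputs from the protocol article.** SMD 0.3 (or 0.2), alpha 0.05, beta 0.20, N = 352 (or 787) and dropout of about 20% come from *Sample size estimation*. Two-sided testing, the week-8 SD as scale, and the model come from *Primary analyses*. Balance over 16 combinations makes each component a 1:1 comparison.

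**1. Reproducing the targets.** For a 1:1 comparison with SD 1, n per group = 2(1.960 + 0.842)²/d².
- d = 0.3: 2 × 7.849/0.09 = 174.4, rounded up to 175; total 350. The next multiple of 16 is 352.
- d = 0.2: 2 × 7.849/0.04 = 392.4, rounded up to 393; total 786. The t-test version gives 786.8, hence 787.

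Both targets are matched with no dropout, covariate or repeated measures. One-sided testing (276; 620) and 90% power (468; 1052) do not match.

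**2. Power after 20% loss, before baseline adjustment.** SE = 2/√N; power = Φ(d/SE − 1.960).

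| N with week-8 data | d | SE | d/SE | Power |
|---|---|---|---|---|
| 352 | 0.3 | 0.1066 | 2.81 | 80.4% |
| 352 × 0.8 = 281.6 | 0.3 | 0.1192 | 2.52 | 71.1% |
| 787 | 0.2 | 0.0713 | 2.81 | 80.1% |
| 787 × 0.8 = 629.6 | 0.2 | 0.0797 | 2.51 | 70.9% |

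The effect detectable with 80% power is 2.802 × SE: 0.334 at about 282 and 0.223 at about 630.

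**3. Does the repeated-measures saving apply?** I computed the generalised least squares information for the week-8 contrast under nominal visits and unstructured covariance. With complete data its variance, relative to a week-8-only analysis, is 1.000 whether there are 2 or 8 post-baseline visits. Extra visits therefore save nothing.

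With dropout, earlier visits recover part of the loss. The amount depends on correlations and dropout timing, which are assumptions here. Without the baseline term, power for 352 is:
- 71.1% if all dropout precedes the first post-baseline visit;
- 71.9–77.0% with dropout spread evenly over visits, across the structures tried;
- at most 79.5% if only the week-8 assessment is missed.

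**4. The baseline covariate.** The SMD is scaled by the unadjusted week-8 SD, so adjustment multiplies the SE by √(1 − ρ²), where ρ is the correlation between baseline and week-8 PHQ-9. The article gives no ρ. With 281.6 analysable and d = 0.3:

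| ρ (assumed) | Power |
|---|---|
| 0.3 | 75.1% |
| 0.4 | 78.4% |
| 0.447 | 80.3% |
| 0.5 | 82.8% |

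Break-even is where 1 − ρ² = 0.8, so ρ = √0.2 = 0.447. Results for 630 at d = 0.2 are nearly identical (74.9%, 78.2%, 80.1%, 82.6%).

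**5. Both effects together.** Assume eight weekly visits, 20% dropout spread evenly, and a first-order autoregressive correlation extended back to baseline. Power for 352 is then:

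| Adjacent-week correlation | Implied ρ | Without baseline | With baseline |
|---|---|---|---|
| 0.76 | 0.11 | 72.8% | 73.2% |
| 0.85 | 0.27 | 74.0% | 76.8% |
| 0.90 | 0.43 | 75.1% | 82.3% |
| 0.95 | 0.66 | 76.7% | 93.9% |

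**The case against.** The strongest reply is that 71–77% is not the power of the planned analysis. Baseline PHQ-9 is in the primary model, and the high within-person correlation that lets the MMRM recover lost information also tends to make that covariate useful. Step 5 bears this out: the planned model runs from about 73% to 94% over the range tried. This stands. A reader might infer that the trial is underpowered, with true power of 71–77%. The documents do not support that, because those figures leave out a term the plan includes. They do not support the opposite either, because no correlation is given and the sample size section never invokes the covariate.

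A second reply is that 20% may not mean missing week-8 scores. Randomisation follows completion of the psychoeducation run-in, and outcomes are still collected after the intervention stops, with reminders and payment. Actual loss could indeed be lower. But *Termination rules for participants* says that someone taken off treatment is not counted as having dropped out and is still assessed. The section also answers dropout with an analysis method for missing outcomes. Lost outcome data is the natural reading, and 20% is the plan's own figure.

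Third, the visit schedule table is not reproduced in the text at hand, so the eight weekly visits are assumed. That affects how much the MMRM recovers. It does not affect the complete-data result in step 3.

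**Conclusion.** Two points are firm. Neither target contains a dropout allowance, and the stated reason for omitting one does not fit the primary analysis. On the basis written, the 80% power is unsupported and the size is not conservative.

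The shortfall is conditional. If 20% of week-8 scores are lost and no baseline adjustment is credited, power is about 71% for each target. For 352 it is roughly 71–77% once partial MMRM recovery is counted, with dropout spread over visits and assumed correlations. An SMD of 0.33 is what about 282 analysable participants detect with 80% power. With the planned covariate, power reaches 80% if the baseline to week-8 correlation is about 0.45 or more, so true power may lie on either side of 80%.

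This is a wrong justification and an unsupported power statement. The allocation, the model and the choice of endpoint are not at fault.

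**What to change.** In *Sample size estimation*:

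1. Delete the sentence on the 30–50% saving and the word *conservatively*.
2. State the expected analysable numbers after 20% loss, about 282 of 352 and about 630 of 787. Give the unadjusted power (about 71% at SMD 0.3 and 0.2 respectively) or the detectable effect (about 0.33 and 0.22). Say that the 20% refers to missing week-8 PHQ-9 scores, if that is what is meant.
3. If 80% power is to be kept, base it on the baseline PHQ-9 covariate, with a stated and justified baseline to week-8 correlation (about 0.45 or more if week-8 loss is 20%).

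This rewords one paragraph. The only cost is a less favourable stated power; the design, the analysis and the number of patients stay as they are.

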### Monitoring

#### Data monitoring

Data integrity will be monitored centrally, first through the built-in data check system on the server program and second by the data management center on a monthly basis. The data management center will prepare the monthly summary (the number of participants entering the study, the number of participants completing the study, and serious adverse events) to be presented. Since the psychological intervention provided by the application is not invasive or expected to cause serious harm, a data monitoring committee will not be organized.

#### Harm

No specific or serious adverse events are expected for the participants who use this smartphone app. However, using it might lead to psychological distress in some participants, depending on their psychological state. We evaluated these potential adverse events by qualitative evaluation of the intervention in a previous study.

#### Compensation

Our previous trials suggest that a little harm occurred in this trial. However, if any health hazards occur, they will be covered by the National Health Insurance system.

#### Auditing

Because the intervention can be classified as a “minimally invasive intervention,” no formal auditing will be conducted.

## Ethics and dissemination

### Research ethics approval

The protocol was approved by the Institutional Review Board of Nagoya City University (ID:46-20-0005) and will be approved by the ethics committees of other collaborating universities.

### Protocol amendments

If important protocol modifications are needed, the investigators will discuss and report them to the Institutional Review Board of Nagoya City University for approval. Once approved, they will be reported to all the study investigators and, when necessary, to the study participants. Further approval of the ethics committees of the participating universities will also be sought.

### Confidentiality

Each participant will receive an identification number. All records will be managed using identification numbers. The security of the data transfer between the application and the server will be guaranteed by SSL, and the data will be stored on the secure server. The data management center will download the data regularly and store them using a medium that is not connected to the Internet and is kept in a locked drawer. Once the trial is completed, the data on the server will be erased permanently. The medium storing the downloaded data will be kept in the locked drawer in the student health center for 10 years after the publication of the primary findings.

### Access to data

All members of the steering committee will have full access to the final trial dataset.

### Ancillary and post-trial care

All participants will receive the standard care, except specialized cognitive behavioral therapy, provided by the participating hospitals and corresponding facilities both throughout and after the study.

### Dissemination policy

The protocol paper and the study results will be submitted to peer-reviewed journals. The first author of the main paper will be a member of the steering committee (authors of the protocol paper). If approved by the steering committee, another person could be the first author. The list of coauthors will be determined before submitting each paper. The main and relevant findings will be presented at conferences.

## Patient and public involvement statement

The study protocol was designed with a patient (a breast cancer survivor) who participated in the study as a researcher. She appropriately discussed the protocol with other patients when a patient’s preferences and/or opinions were considered. She will play the same role in implementing the study. Therefore, patients have been and will always be included in the study. The results of the study will be made public on the study homepage.

## Discussion

We have described the protocol of the MOST fully factorial trial aimed at optimizing smartphone psychotherapy for cancer patients. The primary objective of this study is to develop the most efficient and effective smartphone psychotherapy package to address depression and anxiety in cancer patients after diagnosis to improve their quality of life. As the usability of iCBT in cancer patients has not been shown, this study will be the first to show it [46].

There will be many challenges in conducting this trial, including the recruitment of participants and their retention in the smartphone psychotherapy intervention and assessment. We have taken the following measures to address these challenges. First, we will sample patients in several high-volume cancer centers and university hospitals and ask oncologists to directly invite their patients using leaflets. Second, we have incorporated several trial design features to increase retention: the run-in period occurs before randomization so that only those who have shown preliminary adherence to the program are randomized; measuring the primary outcome at a relatively early time point (2 months); assessing all the outcomes online with several prompts built into the smartphone app; and offering appropriate monetary incentives, as approved by the ethics committee, for the completeness of data collection. In addition, we will send an e-mail to the participants who do not answer the questionnaire before the deadline. Finally, the research team has a good track record in enrolling and following participants in previous trials.

The merit of this study is that it is the first research aimed at precision medicine to determine what kind of psychotherapy, in what combination and in what order it should be provided to the vast number of cancer patients who are not receiving appropriate psychotherapy. If an effective combination of psychotherapy is determined in this study, it can be provided using smartphones to patients who cannot easily access hospitals or clinics. Considering future developments, it may be necessary to consider the appropriate targets.

We will begin recruiting in 2021 and aim to complete the trial by 2023. The results will be published soon after.

## Patient consent

Not needed.

## Trial status

This is version 1.1 of the protocol. Recruitment started on March 1, 2021, and is expected to be completed in March 2023.

## Data Availability

After the publication of the primary findings, the deidentified and completely anonymized individual participant-level dataset will be posted on the UMIN-ICDR website (http://www.umin.ac.jp/icdr/index-j.html) so that it can be accessed by qualified researchers.

## Abbreviations

AT: Assertion training
BA: Behavioral activation
CBT: Cognitive behavioral therapy
EDC: electronic data capturing
e-PRO: electronic patient-reported outcome
GAD-7: Generalized Anxiety Disorder-7
ITT: Intention-to-treat
MOST: Multiphase optimization strategy
PE: Psychoeducation
PHQ-9: Patient Health Questionnaire-9
PS: Problem solving
RCT: Randomized controlled trial
SSL: Secure Socket Layer
